### Cluster randomized-controlled trial

This is a two-group, non-blinded cluster RCT conducted in the primary health centers in Burkina Faso and the DRC (see Fig. 2 for the cluster RCT flow diagram, and Fig. 3 for the schedule of enrolment, interventions, and assessments (SPIRIT template)). Randomization to control and intervention arms is at the level of the health center. Participants allocated to the experimental group will receive the PPFP intervention package and those allocated to the control group will receive usual care. Service providers who have midwifery and contraceptive skills and who offer ANC, delivery, and PNC services will implement the clinical components of the PPFP package. The cluster RCT design is justified by the fact that the different components of the PPFP intervention package, which will eventually be identified, may not be delivered directly to individual participants but only applied at the level of the health center (e.g. refresher training for service providers, optimization of health service organization).

**Fig. 2 Fig2:**
[figure not shown]
Flow diagram of the cluster randomized control trial in each study country

**Fig. 3 Fig3:**
[figure not shown]
Schedule of enrolment, interventions, and assessments for the cluster randomized controlled trial phase in each study country (SPIRIT template)

#### Outcome measures

Case-report forms (CRFs) will be developed for quantitative indicators. The primary outcome is the uptake of modern contraceptive methods at twelve months postpartum (proportion of women using modern contraceptives at twelve months in the experimental vs. control group).

Secondary outcomes include: use of a modern contraceptive method upon clinic discharge (24–48 h), at six days, six weeks, six months, and nine months postpartum. Intermediate outcomes include the decision taken at different follow-up points to use a contraceptive method. The proposed postpartum follow-up schedule is in line with current national practices in both study countries, although it is slightly different from those recommended by WHO [53]. In 2013, WHO issued the following recommendations for the timing of postnatal visits: on day 1 (24 h), on day 3 (48–72 h), between days 7 and 14, and at week 6.

#### Process measures

It is important to note that the cluster RCT is designed to evaluate the effectiveness of a package of PPFP interventions and cannot indicate which specific intervention in the package will have the most impact on postpartum contraceptive uptake. Therefore, we plan a process evaluation with the objectives to: (1) detect implementation issues that could be explanatory in case the intervention is not effective; and (2) facilitate the replication and scale-up of the intervention if it is proven effective. We have therefore developed process indicators in the CRFs to help assess the level of implementation of selected interventions of the package. Event logs and monitoring visit checklists implemented at health centers will offer other sources of process-oriented information. The qualitative research embedded in the intervention phase will further contribute to understanding the barriers and enablers related to the delivery of PPFP and to the implementation of the trial. The process indicators and the embedded qualitative research will give clues as to the components of the package that participants and providers will perceive as having a greater impact.

#### Sample size calculation

The sample size is estimated based on the following assumptions: among women at six months postpartum, DHS data report 7.2% of use of any method (modern or traditional) in Burkina Faso [56] and 5.1% of use of modern methods in the DRC [10]. These figures allow us to assume that around 5.0% of participants in the control group in both countries will adopt a modern contraceptive at six months postpartum. In Burkina Faso and the DRC, women in the general population have a similar contraceptive prevalence rate for modern methods of 15.0%, which allows us to assume that around 15.0% of participants in the experimental group will use a modern method at six months postpartum. Given the high unmet need for PPFP, we assume that an increased proportion of at least 20.0% of participants in the experimental group will adopt a modern method at twelve months postpartum. This corresponds to a difference of 15.0% between the experimental group (20.0%) and the control group (5.0%). Therefore, assuming an intra-cluster (health center) correlation coefficient of 0.02, we used PASS 11 Software (Power Analysis and Sample Size) for sample size calculation: the experimental group and the control group will each have four study sites with at least 60 participants per site in each study country [57]. This allows for a statistical power of 93% to detect a difference of 15% to a level of significance of 5% at the individual level (and not at the facility level). Assuming a 10% participant loss to follow up, each site will recruit at least 70 pregnant women. This equates to a cohort of 280 pregnant women in each group (4 sites × 70 participants), and in total 560 participants per country (280 participants × 2 study groups). Therefore, across both countries, the study will have a total sample size of 1120 participants (560 in the experimental and 560 in the control group).

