#### Randomization

In each country, the eight sites are matched by pairs according to (1) the average number of deliveries per month; (2) the ratio of health workers per population; and (3) the settings (rural, urban). Within each of the four pairs, we will randomly select the site assigned to the experimental intervention. This randomization is performed four times (once for each pair) in each study country. No restriction in the randomization process is required and masking cannot be done. All consecutive and eligible participants will be included in the clusters.

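### The stated per-country power of 93% makes no allowance for only four randomized centers per arm: a test that holds its 5% level has about 82%, or 64–91% if the pairs are analyzed

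*Protocol article*

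**What the plan says.** The Sample size calculation section of the protocol article sets the layout by country: "the experimental group and the control group will each have four study sites with at least 60 participants per site in each study country". The target is that "at least 20.0% of participants in the experimental group will adopt a modern method at twelve months postpartum", against 5.0% in the control group, "assuming an intra-cluster (health center) correlation coefficient of 0.02". The resulting claim is: "This allows for a statistical power of 93% to detect a difference of 15% to a level of significance of 5" per cent, with the qualifier that this is "at the individual level (and not at the facility level". For attrition it adds: "Assuming a 10% participant loss to follow up, each site will recruit at least 70 pregnant women". The section then totals 560 women per country and 1120 over both countries.

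The Randomization section says that the eight sites in each country are matched in pairs on delivery volume, staffing ratio and rural or urban setting, and that "Within each of the four pairs, we will randomly select the site assigned to the experimental intervention". The Statistical analysis section takes the participant as the unit of analysis with the intra-cluster correlation accounted for, and defers the detail to a statistical analysis plan that is not shown. It does not say whether the primary comparison is made in each country or over both.

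**The concern.** Applying a design effect enlarges the variance correctly. Referring the result to 1.96, however, treats the between-center variance as known. In one country it is estimated from eight centers, four per arm. A test based on that country's centers alone needs a t reference with 2 × (4 − 1) = 6 degrees of freedom, or 4 − 1 = 3 if it works on the four within-pair differences. The critical values are then 2.447 and 3.182.

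At stake is how a country-level result is read. A null result would be judged against a stated 7% chance of missing the target effect. On the same inputs the chance is about 18% with 6 degrees of freedom, and between 9% and 36% for a paired analysis.

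**Working it through.** **Inputs**, all from the Sample size calculation section unless noted: control 5%, experimental 20%, intra-cluster correlation (ICC) 0.02, 60 evaluable women per center, 4 centers per arm per country, significance 5%. Two-sided testing is assumed. The four pairs per country come from the Randomization section.

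**Reproducing 93%**
- Design effect = 1 + (60 − 1) × 0.02 = 2.18.
- Women per arm = 4 × 60 = 240, so the effective number is 240/2.18 = 110.1.
- Binomial variances: 0.05 × 0.95 = 0.0475 and 0.20 × 0.80 = 0.16; sum 0.2075.
- SE = √(0.2075 × 2.18/240) = √0.0018848 = 0.0434.
- Signal to noise = 0.15/0.0434 = 3.455.
- Power = Φ(3.455 − 1.96) = 93.3%. With the pooled null variance it is 92.5%.

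So 93% is the two-sided z-test figure for four centers per arm. The same z calculation with eight centers per arm (both countries) gives 99.8%, which confirms that 93% is the per-country claim.

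**Allowing for the number of centers** (noncentral t, two-sided 5%, noncentrality 3.455)
- Pairs ignored, 6 degrees of freedom, critical value 2.447: **81.9%** (80.0% with the pooled variance).
- Paired, 3 degrees of freedom, critical value 3.182, matching removing no between-center variance: **64.1%**.

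**Gain from matching.** Split the variance of the difference into a within-center part, 0.2075 × 0.98/240 = 0.000847, and a between-center part, 0.2075 × 0.02/4 = 0.001038. If matching removes a share r of the second part, the noncentrality is 0.15/√(0.000847 + 0.001038 × (1 − r)). The 3-degree-of-freedom power is then:

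| r | power |
|---|---|
| 0 | 64.1% |
| 0.3 | 71.2% |
| 0.5 | 76.6% |
| 1 | 91.3% |

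Even perfect matching stays below 93%.

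**Simulation check** (200,000 beta-binomial trials, same inputs, cluster-level tests): 82.9% for the unpaired t-test and 65.0% for the paired one. With a true null (5% in both arms), referring the unpaired statistic to 1.96 rejects in 9.4% of trials, so the z reference does not hold the 5% level for which the 93% is quoted. With 2.447 the rejection rate is 4.7%.

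**Recruitment margin.** 70 women less 10% leaves 63 per center. Power is then 82.7% (6 degrees of freedom) and 65.0% (3, no matching gain). With all 70 retained it is 84.3% and 66.8%.

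**Both countries pooled** (8 centers per arm): noncentrality 0.15/√(0.2075 × 2.18/480) = 4.886. Power is 99.5% with 14 degrees of freedom and 98.6% with 7 (eight pairs, no matching gain).

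**The case against.** The strongest reply is that nothing has been miscalculated: clustering is in the calculation, the software is named, and 93% is right for the method behind it. That stands. The fault is in the reference distribution, not in the arithmetic.

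A second reply is that the article fixes no test, and that small-sample corrections and the handling of pairs belong in the statistical analysis plan. This is true of the analysis model. The power figure, however, is stated here, and neither t-based analysis above reaches 93% on these inputs, whatever the gain from matching.

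Third, sidedness is not stated. A one-sided 6-degree-of-freedom test would have 91.8%, close to the claim but still short of it. The 3-degree-of-freedom equivalent, with no matching gain, is 82.9%.

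Three stronger readings are tempting and are not supported:
- A reader might infer that the trial is underpowered. It is not, if the countries are pooled: the pooled comparison has about 99% even with small-sample degrees of freedom, and the article does not say that the primary comparison is per country.
- A reader might take 64% as the true per-country power. It is a lower bound that needs both a paired analysis, to which the article does not commit, and matching factors that explain no between-center variance, although they were presumably chosen because they might.
- A reader might take the phrase "at the individual level (and not at the facility level" to mean that clustering was ignored. The ICC is applied in the same section, and the phrase can fairly be read as naming the unit of analysis, in line with the Statistical analysis section.

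**Conclusion.** The point holds for the stated per-country figure and no further. The 93% is a large-sample value that does not allow for four randomized centers per arm. On the plan's own inputs a two-sided 5% test within one country has about 82% power with the pairs ignored, 11 percentage points below the claim. With the pairs analyzed it has 64% to 91%; where in that range cannot be settled, because the article gives no matching correlation. Analyzing individual women with an adjustment for the ICC is legitimate, but it adds no randomized units and so does not lift this limit.

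The conclusion assumes two-sided testing, a between-center variance estimated from that country's centers only, and the plan's values of 5%, 20% and 0.02.

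**What to change.** In the Sample size calculation section:
- Restate the per-country power as about 82% (6 degrees of freedom, pairs ignored). If the pairs will be analyzed, give a value within 64–91% together with the matching gain assumed.
- Put the pooled two-country power beside it: 99.5% with 14 degrees of freedom, or 98.6% with 7.
- State that the test is two-sided, if that is intended.
- Clarify that the individual-level wording names the unit of analysis and does not remove the limit set by the number of randomized centers.

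This is a text change. It needs no extra centers or women; the only cost is a less favourable stated figure for each country.

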#### Eligibility criteria for clusters (health centers) and participants (women)

The study will be conducted in eight primary health centers in each country. The eligibility criteria of health centers were described above under the objective of the pre-formative phase. All pregnant women will be eligible to participate in the study if (1) they are in their third pregnancy trimester; (2) the status of the pregnancy and of the woman allows for a birth at the health center; (3) the woman has the intention to attend ANC, delivery, and PNC at the health center; (4) the woman does not participate in another study; and (5) an informed consent is obtained.

#### Interventions

The health centers of the experimental group will implement the PPFP intervention package. The control group will implement usual care. Depending on the nature of the final package, some interventions may be implemented before participant recruitment (such as PPFP refresher training for service providers), while others will be implemented afterwards (such as using the PPFP counseling tool with participants).

#### Randomization

In each country, the eight sites are matched by pairs according to (1) the average number of deliveries per month; (2) the ratio of health workers per population; and (3) the settings (rural, urban). Within each of the four pairs, we will randomly select the site assigned to the experimental intervention. This randomization is performed four times (once for each pair) in each study country. No restriction in the randomization process is required and masking cannot be done. All consecutive and eligible participants will be included in the clusters.

#### Data source and collection

Data on key outcome measures as well as quantitative process indicators will be collected on paper-based CRFs. The WHO team in Geneva will develop the CRFs with inputs from the country research teams. We will test advanced drafts with an appropriate sample of service providers and mock clients from the formative phase sites before finalizing the forms. Each health center of the cluster RCT will have a research assistant who will be trained to adhere to the study manual and standard operating procedures for data management which are common to both study countries and have been developed by WHO. The information reported on the CRFs will be checked for accuracy and completeness several times at different levels by field coordinators and data managers.

#### Data management

As for other multicenter trials conducted and sponsored by the UNDP/UNFPA/UNICEF/WHO/World Bank Special Programme of Research, Development and Research Training in Human Reproduction (HRP) at WHO in Geneva, we will perform data entry and data quality monitoring using a web-based data management system. The Biostatistics and Data Management team at HRP will develop it through OpenClinica (version 3.11), an electronic data capture software for clinical research, which includes programmed edit checks for data accuracy, completeness, and consistency, reduces delays in data queries and problem resolution, and allows the dataset to be quickly available. The OpenClinica system is a highly secure, open-source, and reliable web-based software solution, which is fully compliant with Good Clinical Practice (GCP) and regulatory guidelines and HRP/WHO Standard Operating Procedures for clinical trial managements.

Data entry will be performed locally in Ouagadougou and Kinshasa by the collaborating research centers and checked by the WHO team in Geneva. We will train the country teams in data entry and data management using the OpenClinica system. Country research teams will be responsible for verifying the data, uploading them onto shared files and entering the data into the OpenClinica system. To reduce errors, double data entry will be performed. The system will automatically generate queries on data (missing values, outliers, inconsistencies, and other errors). The WHO team will monitor data quality. Questions about data inconsistencies or missing values will be sent to sites using standardized forms and will be resolved on an ongoing basis. Data transmission will be encrypted to ensure data integrity and confidentiality of participants. Access to the data will be password protected: only authorized users will be allowed access to the data.

#### Statistical analysis

We will prepare a comprehensive statistical analysis plan before finishing recruitment for the study. The participant will form the unit of analysis and intra-cluster correlation coefficient will be accounted for. All analysis will be by intention to treat. We will perform descriptive statistics by computing means, standard deviations, and minimum and maximum values for continuous variables, and frequencies and percentages for categorical variables. As part of quality control and descriptive analysis of the data, we will examine the distribution of variables to detect outliers. Descriptive statistics will be tabulated for individual clusters and aggregated across clusters. We will use IBM SPSS Statistics 21, R, STATA 13, or SAS statistical packages for the analysis. We will present the results according to the 2010 CONSORT Statement checklist and its extension for cluster studies [58].

#### Intervention fidelity

Threats to the PPFP intervention package fidelity will be minimized by providing an initial training to service providers of the experimental sites and ongoing monitoring and supportive supervision visits to assess adherence to the intervention package. The WHO coordination team will hold weekly teleconferences with each country team and conduct periodic site visits to assess implementation progress. An action plan will be implemented if there are any concerns regarding adherence to the intervention package.

### Ethics

In the design of this trial we have taken into account the recommendations provided by The Ottawa Statement on the Ethical Design and Conduct of Cluster Randomized Trials [59]. This protocol was peer-reviewed by the Research Project Review Panel (RP2) of the HRP. RP2 and the WHO Research Ethics Review Committee, Geneva, Switzerland, approved the study protocol as well as the respective ethical committees in Burkina Faso (see Declarations for details). Upon completion of the formative phase, we will submit to the same global and local ethical committees the amendments to the protocols, which will include the finalized PPFP intervention package and the related research instruments for the experimental phase.

## Discussion

Despite the proven benefits of modern contraceptive use, the unmet need for postpartum family planning remains unacceptably high. This is puzzling as survey findings continue reporting that most couples wish to space their children by at least two years [60], and women access health services more often during pregnancy, delivery, and the first year of their child’s life than other periods. During the multiple opportunities given by this heightened contact with health services, we would expect an increase in demand for and supply of contraceptive information and services.

Given the known reliance on amenorrhea from breastfeeding and abstinence for protection from pregnancy for up to a year postpartum, is it then worth investing energy and resources into PPFP programming during the first year postpartum? Despite these practices, DHS data show that the unmet need for PPFP in Burkina Faso and the DRC, as well as in Sub-Saharan Africa in general, remains critically high and it is important to explore the optimal programmatic approaches to address and resolve it. To this end, different strategies have been explored:

First, there has been a renewed interest on highly effective long-acting and reversible methods, such as immediate postpartum IUD. These programs have shown promising results, although they require major undertaking in terms of logistics, competency training of health staff, and demand creation [37]. Burkina Faso and the DRC have recently given commitments to piloting such programs.

Second, targeted investment to promote LAM for up to six months and switching to another method appears justified from the RMNCH perspective. Tabulations of DHS data on exclusive breastfeeding from Burkina Faso and the DRC are not encouraging and reflect the situation in other low-income countries [61]. The median duration of exclusive breastfeeding changed minimally in Burkina Faso between 1993 and 2010 (0.4 and 0.6 month respectively), and in the DRC between 2007 and 2013–14 (1.4 and 2.2 months respectively). This may be due to widespread early supplementation practices that are entrenched by traditions and hard to influence. The median duration of amenorrhea is twelve months in both countries and suggests that breastfeeding, although not exclusive, must be frequent enough to induce an amenorrheic state. Therefore, having health staff promoting LAM at length may not be an efficient use of limited resources.

Third, with a median duration of postpartum abstinence close to eight months in both study countries, it appears that the immediate postpartum or the six-week postpartum visit dedicated to contraceptive services may not respond to women’s demand. Instead of the targeted “high-dose, low-frequency” strategies that promote a method over another and restrict services to a narrow window period, a “low-dose, high frequency” approach during the end of pregnancy and the first year postpartum to deliver contraceptive information and services may be a more appropriate pathway to respond to the wishes and situations of each postpartum woman and couple: giving information to women and couples, including on benefits and limitations of PPFP and of available contraceptive methods, and letting them choose.

The latter choice-based strategy underpins our health service trial, which also stands out for other reasons. First, given the growing availability of ANC, delivery, and PNC services in primary health centers in low-resource countries, we believe that there is an urgent need to design, test, and scale up effective, affordable, and sustainable PPFP interventions that are not only respectful of the intentions, decisions, and situations of clients but that can also reinforce the existing RMNCH continuum of care. This will allow to minimize missed health services opportunities to address the contraceptive needs of postpartum women and couples. Second, due to the complex social, cultural and religious challenges and opportunities surrounding contraceptive use, our research assumes that this can only be accomplished by following participatory action research principles. Engaged stakeholders include adolescents, women, men, key community members, health staff, policy-makers, and researchers, whose views and inputs will contribute to shaping the PPFP intervention package.

Several changes may happen as a consequence of the study. At the individual level, knowledge, attitudes, and behaviors of women and couples toward PPFP will likely be influenced by a set of inexpensive interventions. At the health service delivery level, implementation of the intervention phase will probably require a shift in behavior and accountability of service providers with regard to the systematic integration of PPFP into their clinical practice, and optimization of health service organization to ensure a reliable availability of competent staff and contraceptive methods and supplies when they are needed.

